## Abstract

**Background:**

Cognitive behavioural therapy is an effective treatment for depression. However, one third of the patients do not respond satisfactorily, and relapse rates of around 30 % within the first post-treatment year were reported in a recent meta-analysis. In total, 30–50 % of remitted patients present with residual symptoms by the end of treatment. A common residual symptom is rumination, a process of recurrent negative thinking and dwelling on negative affect. Rumination has been demonstrated as a major factor in vulnerability to depression, predicting the onset, severity, and duration of future depression. Rumination-focused cognitive behavioural therapy is a psychotherapeutic treatment targeting rumination. Because rumination plays a major role in the initiation and maintenance of depression, targeting rumination with rumination-focused cognitive behavioural therapy may be more effective in treating depression and reducing relapse than standard cognitive behavioural therapy.

**Method/design:**

This study is a two-arm pragmatic randomised controlled superiority trial comparing the effectiveness of group-based rumination-focused cognitive behaviour therapy with the effectiveness of group-based cognitive behavioural therapy for treatment of depression. One hundred twenty-eight patients with depression will be recruited from and given treatment in an outpatient service at a psychiatric hospital in Denmark. Our primary outcome will be severity of depressive symptoms (Hamilton Rating Scale for Depression) at completion of treatment. Secondary outcomes will be level of rumination, worry, anxiety, quality of life, behavioural activation, experimental measures of cognitive flexibility, and emotional attentional bias. A 6-month follow-up is planned and will include the primary outcome measure and assessment of relapse.

**Discussion:**

The clinical outcome of this trial may guide clinicians to decide on the merits of including rumination-focused cognitive behavioural therapy in the treatment of depression in outpatient services.

**Trial registration:**

ClinicalTrials.gov Identifier: NCT02278224, registered 28 Oct. 2014.

## Background

Cognitive behavioural therapy (CBT) is a recommended treatment for unipolar depression, and a large number of studies provide supportive evidence for its efficacy in both an individual as well as a group format [1–3]. CBT has been shown to be effective in the short term and to have enduring effects in reducing the risk of returning symptoms after treatment has ended. However, approximately one third of the patients do not respond satisfactorily to the treatment [4, 5], and post-treatment residual symptoms are a common problem; as many as 30–50 % of remitted patients experience residual symptoms at the end of treatment [6]. Residual symptoms of depression are associated with ongoing psychosocial and functional disability and have been demonstrated to predict poorer long-term outcome of major depression, including increased rates of relapse [7–9]. A recent meta-analysis reports relapse rates of around 29 % within 1 year and 56 % within 2 years [10].

Recent studies have evaluated the potential benefit of continuation-phase CBT in reducing residual symptoms as well as in preventing subsequent depressive relapse or recurrence. In general, continuation-phase cognitive therapies have proven to be beneficial in reducing rates of relapse and recurrence [10]. Yet, in most of these studies, only a modest reduction in residual symptoms was observable [11, 12], indicating the possibility of further improvement in efficacy by targeting key residual symptoms. With the aim of improving efficacy, an increased focus has been directed toward a common residual symptom, namely depressive rumination [13, 14]. Rumination is a passive process of recurrent negative thinking and dwelling on negative affect, causes, and symptoms [15] and has been shown to be a major factor in vulnerability to depression as well as predicting the onset, severity, and duration of future depressive episodes [16, 17]. Consequently, if involved in the pathogenesis of depression, rumination may constitute a relevant target for psychological intervention. In support of this, recent psychotherapeutic interventions designed to target depressive rumination show promising results [18–20]. The strongest evidence thus far exists for the rumination-focused cognitive behavioural therapy (RFCBT) developed by Watkins and colleagues [18]. RFCBT is based on a conceptualization of repetitive thinking that differentiates between a functional and a dysfunctional style of thinking. The helpful style is characterized by being concrete and specific, whereas the unhelpful style is abstract and evaluative and does not lead to problem solving (rumination) [21]. In RFCBT, rumination is formulated as a habitual behaviour controlled by the laws of behavioural psychology [22] and maintained by negative reinforcement. Rumination can act as a form of avoidance by thinking about difficulties rather than confronting them directly in the real world and thereby avoiding the risk of failure and negative outcomes. Hence, rumination can become reinforced by escape and avoidance. Grounded in behavioural psychology and research, RFCBT focuses on functional analyses of the target behaviour, rumination, and combines strategies from behavioural activation with novel strategies to foster concrete, process-focused, and specific thinking. RFCBT differs from standard CBT by focusing on modifying the process of thinking, whereas CBT focuses on modifying the content of the thoughts and content of dysfunctional schemas [14]. With only a handful of trials conducted, the evidence for RFCBT is still sparse, although it is promising. For example, in a recent clinical trial with patients with medication-refractory residual depression, 42 patients were randomly allocated (1:1) to treatment-as-usual (TAU) consisting of continuation anti-depressants and outpatient clinical management or to TAU plus up to 12 sessions of individual RFCBT. RFCBT was found to be superior to TAU; 62 % of patients in the RFCBT treatment condition achieved remission, compared with 21 % in the TAU [18]. However, to date, no study has made a direct comparison of RFCBT with standard CBT. The aim of the present study is to compare group-based rumination-focused cognitive behaviour therapy (g-RFCBT) with group-based standard cognitive behavioural therapy (g-CBT) for depression on the effectiveness of treatment and the reduction of relapse rates at 6-month follow-up.

## Methods/design

This study is a two-arm pragmatic randomised controlled trial comparing the effectiveness of g-RFCBT with the effectiveness of g-CBT for treatment of depression. Our primary hypothesis is that g-RFCBT will be superior to g-CBT in reducing depressive symptoms measured on the score on the Hamilton Rating Scale for Depression (HRSD) at the end of treatment. Our secondary hypothesis is that g-RFCBT will be superior to g-CBT in reducing relapse at 6-month follow-up after the end of treatment. Relapse is defined as a score of 13 points or more on the HRSD.

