### Eligibility criteria

Patients who are between 18 and 65 years of age and who meet Diagnostic and Statistical Manual of Mental Disorders, 4th Edition (DSM-IV) criteria for a current episode of unipolar major depression or recurrent or chronic depression in a structured M.I.N.I. 5.0 interview and with a score of 13 or more on the 17-item HRSD can be included [18]. Patients with psychotic symptoms, bipolar disorder, functional illiteracy, or alcohol and drug abuse will be excluded. Patients with depression and co-morbid anxiety or personality disorder are included in the study. Patients receiving anti-depressants will not be excluded.

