### Recruitment

The study takes place in a community psychiatric outpatient service in Hillerød, Denmark, which treats 200–250 patients with diagnosed depression per year. Patients who are referred for treatment with a primary diagnosis of depression, recurrent or chronic, will be recruited to the study. We plan to recruit a total of 128 patients, 64 in each treatment arm.

The psychiatrist conducting the initial evaluation of the patients will invite the patients to talk to the researcher if the inclusion criteria are met. Written informed consent will be obtained from all patients prior to enrolment in the study. The researcher will validate the depression diagnosis and screen for DSM-IV Axis I co-morbidity by using the structured International Neuropsychiatric Interview M.I.N.I. version 5.0 [23] and for DSM-IV Axis II disorders by using the Standardized Assessment of Personality-Abbreviated Scale, an eight-item semi-structured interview screening for the presence of a personality disorder [24]. Patients meeting the inclusion criteria will be included in the study, and baseline assessment will be conducted within 2 weeks prior to commencement of the psychotherapeutic treatment. After the baseline assessment, the patients are randomly assigned to receive one of the two treatment options.

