#### Secondary outcomes

Secondary outcomes will be conducted post-treatment by using the following measures. The Hamilton Depression Rating Scale (HAM-D6) is a six-item self-report rating scale (corresponding to the 17-item observer-rated HRSD), which measures the core symptoms of the depression construct on a unipolar scale. The HAM-D6 questionnaire has been shown to be a reliable and valid measure of the severity of depressive symptoms in a clinical sample [32]. The Behavioural Activation for Depression Scale (BADS) is a 25-item questionnaire measuring changes in avoidance and activation over the course of behavioural activation and has been shown to be reliable and valid in a community sample with elevated depressive symptoms [33]. The Penn State Worry Questionnaire (PSWQ) is a 16-item questionnaire assessing the general trait of worry and has been shown to be reliable and valid in a clinical sample [34]. The Rumination Response Scale (RRS) is a 22-item self-report measure that assesses ruminative response to depressive symptoms. Participants are asked to indicate the frequency of rumination with the total score indicating the severity of rumination used as a strategy in response to depressive symptoms [35]. The Generalised Anxiety Scale (GAD-7) is a seven-item questionnaire assessing the severity of symptoms of generalised anxiety disorder. GAD-7 has been shown to be valid in a community sample [36]. The World Health Organization Well Being Index (WHO-5) is a five-item questionnaire assessing the level of well-being [37]. The Trail Making Task A and B is a neuropsychological test of visual attention and task switching. It consists of two parts in which the test respondent is asked to connect 25 dots as fast as possible while still maintaining accuracy [38]. The Dot Probe Task is a non-verbal computerized task assessing the level of visual attentional bias from emotional pictures [39]. Furthermore, assessment with Dot Probe Task, HAM-D6, RSS, PSWQ, and BADS will take place after the fourth and the eighth sessions. A 6-month post-treatment follow-up will be conducted to measure the level of depressive symptoms with HRSD, and depressive relapse will be assessed by a diagnostic interview based on DSM-IV criteria for depression.

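### Relapse is defined in two incompatible ways, and the HRSD rule also counts patients who never improved, so it measures depressed status at 6 months rather than relapse alone

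*Protocol article*

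**What the plan says.** All references are to the protocol article.

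- **Methods/design** sets the hypothesis: "Our secondary hypothesis is that g-RFCBT will be superior to g-CBT in reducing relapse at 6-month follow-up after the end of treatment". The next sentence gives the rule: "Relapse is defined as a score of 13 points or more on the HRSD".
- **Secondary outcomes** gives the two 6-month measurements separate jobs. For the scale: "A 6-month post-treatment follow-up will be conducted to measure the level of depressive symptoms with HRSD". For relapse: "depressive relapse will be assessed by a diagnostic interview based on DSM-IV criteria for depression".
- **Eligibility criteria** use the same number for entry. Patients who meet DSM-IV criteria and "with a score of 13 or more on the 17-item HRSD can be included".
- **Background** says that with CBT "approximately one third of the patients do not respond satisfactorily to the treatment". It cites a relapse rate of about 29 % within 1 year and gives no 6-month figure.

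No section requires remission, response or an HRSD below 13 at end of treatment before a patient can relapse. No section says how the score and the interview combine.

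**The concern.** There are two separate faults.

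First, one endpoint has two criteria. A severity score and a diagnostic interview are different instruments. A patient can score 13 or more without meeting DSM-IV criteria, or meet them with a lower score. The eligibility criteria themselves treat the two as distinct, because entry requires both.

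Second, the HRSD rule does not isolate relapse. Every participant has the relapse score at entry. A patient who scores 15 at baseline, 15 at end of treatment and 15 at 6 months counts as a relapse without ever having been better. The rule therefore captures depressed status at 6 months, which is persistence plus return.

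Reducing relapse is part of the trial's stated aim, and the Discussion presents lower relapse rates as something services would welcome. If g-RFCBT improves acute response, as the primary hypothesis expects, the HRSD rule can show fewer relapses even if patients who got better relapse equally often in both arms. It could equally obscure a real difference in relapse.

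**Working it through.** The article states no relapse rate, sample size or power for the secondary hypothesis, so there is no planned figure to reproduce. The finding rests on setting the sections side by side. The arithmetic only shows how large the mixing could be.

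**Inputs**
- *q*, share of patients not below 13 at end of treatment: one third, from the Background. Treating unsatisfactory response as HRSD of 13 or more is an assumption; the article does not make that link. Also varied from 20 % to 40 %.
- *s*, share of these still at 13 or more at 6 months: assumed 50–100 %.
- *r*, relapse by 6 months among the others: assumed 15–29 %. The lower end is close to the half-year equivalent of the cited one-year rate under a constant hazard, 1 − √(1 − 0.29) = 0.157. The upper end places the whole one-year rate within 6 months.
- Patients per arm: "64 in each treatment arm".

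**Composition of the counted relapses**

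Counted share = *qs* + (1 − *q*)*r*. Share of these who never improved = *qs* / [*qs* + (1 − *q*)*r*].

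With *q* = 1/3:

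| *s* | *r* | Counted as relapse | Of these, never improved |
|---|---|---|---|
| 50 % | 15 % | 0.167 + 0.100 = 26.7 % | 62.5 % |
| 50 % | 29 % | 0.167 + 0.193 = 36.0 % | 46.3 % |
| 100 % | 15 % | 0.333 + 0.100 = 43.3 % | 76.9 % |
| 100 % | 29 % | 0.333 + 0.193 = 52.7 % | 63.3 % |

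The rule counts 27–53 % of an arm, or 17 to 34 of 64 patients, and 46–77 % of those never improved.

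Widening *q* to 20–40 %:
- lowest: 0.20 × 0.50 / (0.100 + 0.80 × 0.29) = 0.100 / 0.332 = 30 %
- highest: 0.40 × 1 / (0.400 + 0.60 × 0.15) = 0.400 / 0.490 = 82 %

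**Apparent effect with no difference in relapse**

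If *r* and *s* are equal in both arms and only *q* differs, the difference in counted relapse is (*q* in g-CBT − *q* in g-RFCBT) × (*s* − *r*). Taking 33.3 % versus 20 % as an example:
- *s* = 100 %, *r* = 15 %: 0.133 × 0.85 = 11.3 percentage points (43.3 % versus 32.0 %)
- *s* = 50 %, *r* = 29 %: 0.133 × 0.21 = 2.8 percentage points (36.0 % versus 33.2 %)

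The sign favours the arm with the better acute response whenever non-improvers are more likely to be at 13 or more than improvers are to relapse.

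**Patients truly at risk of relapse**

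64 × 2/3 ≈ 43 per arm, giving about 43 × 0.15 ≈ 6 to 43 × 0.29 ≈ 12 relapses per arm before any dropout.

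**The case against.** The best defence is that this is a condensed article. Relapse ordinarily implies earlier improvement, the hypothesis speaks of the period after treatment ends, and the at-risk population may be set out in a full protocol or analysis plan that is not shown. Since entry combines DSM-IV criteria with the HRSD cut-off, a combined reading of the two relapse statements is also possible. This does not remove the point: the article states a definition and then a different one, and neither section states the combined reading. It does limit what may be concluded.

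Four stronger readings are tempting and are not supported:

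- *That the trial would not measure relapse at all.* This applies only to the HRSD rule read literally. If the interview governs, the answer depends on whether the analysis is limited to patients no longer depressed at end of treatment, which the article does not say.
- *That the definition will be picked after seeing the data.* An analysis plan may already name it. This is a risk, not a fact.
- *That most counted relapses are necessarily patients who never improved.* That depends on how many non-improvers stay at 13 or more. At the low end of the ranges the share is below half.
- *That low power for relapse shows harm from this definition.* The article claims no power for relapse, and events would be few under any definition.

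It is also fair to object that an outcome of staying below 13 at both visits, analysed in all randomised patients, does not separate relapse from non-response. Its failure rate is *q* + (1 − *q*)*r*. At *s* = 100 % these are exactly the patients counted by the HRSD rule, for example 33.3 % + 66.7 % × 15 % = 43.3 %. That objection stands. Such an outcome corrects the label and the permitted conclusion, not the mixing.

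**Conclusion.** The plan is wrong as written on this point. The two sections give relapse different criteria and do not say which governs. The HRSD rule, followed literally, counts patients who never improved. These two conclusions come from the text and need no assumption.

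The size does need assumptions. Under those set out above, 46–77 % of counted relapses would be patients who never improved, or about 30–82 % across the wider range of non-response. The 6-month persistence and relapse rates are not in the article, and the one-third figure is not defined there by the HRSD.

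The damage is confined to the secondary hypothesis. The primary comparison of HRSD at end of treatment and its analysis are unaffected. This should be fixed, but it does not threaten the trial's main result.

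**What to change.** 1. Reconcile Methods/design with Secondary outcomes by naming one governing criterion for relapse, the HRSD score or the DSM-IV interview, with the other as supportive.
2. Use the word relapse only for patients below the trial's own threshold (HRSD below 13) at end of treatment who meet the governing criterion at 6 months. Report this with a confidence interval and the caveat that the subset is formed after randomisation, so the arms are no longer protected by it.
3. For the comparison of all randomised patients, report the outcome under its true name: below the threshold at both end of treatment and 6 months, or depressed status at 6 months. State that it mixes acute response with relapse and cannot by itself support a claim of relapse prevention.

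The cost is an amendment to the wording. The article already schedules the HRSD at end of treatment and at 6 months, and the interview at 6 months, so no new data are needed. The downside is that the randomised comparison no longer carries the label of a relapse rate, and the relapse estimate itself will be imprecise, with roughly 6 to 12 events per arm in the illustration.

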### Eligibility criteria

Patients who are between 18 and 65 years of age and who meet Diagnostic and Statistical Manual of Mental Disorders, 4th Edition (DSM-IV) criteria for a current episode of unipolar major depression or recurrent or chronic depression in a structured M.I.N.I. 5.0 interview and with a score of 13 or more on the 17-item HRSD can be included [18]. Patients with psychotic symptoms, bipolar disorder, functional illiteracy, or alcohol and drug abuse will be excluded. Patients with depression and co-morbid anxiety or personality disorder are included in the study. Patients receiving anti-depressants will not be excluded.

### Recruitment

The study takes place in a community psychiatric outpatient service in Hillerød, Denmark, which treats 200–250 patients with diagnosed depression per year. Patients who are referred for treatment with a primary diagnosis of depression, recurrent or chronic, will be recruited to the study. We plan to recruit a total of 128 patients, 64 in each treatment arm.

The psychiatrist conducting the initial evaluation of the patients will invite the patients to talk to the researcher if the inclusion criteria are met. Written informed consent will be obtained from all patients prior to enrolment in the study. The researcher will validate the depression diagnosis and screen for DSM-IV Axis I co-morbidity by using the structured International Neuropsychiatric Interview M.I.N.I. version 5.0 [23] and for DSM-IV Axis II disorders by using the Standardized Assessment of Personality-Abbreviated Scale, an eight-item semi-structured interview screening for the presence of a personality disorder [24]. Patients meeting the inclusion criteria will be included in the study, and baseline assessment will be conducted within 2 weeks prior to commencement of the psychotherapeutic treatment. After the baseline assessment, the patients are randomly assigned to receive one of the two treatment options.

### Randomisation and concealment

Participants will be allocated in a 1:1 ratio to either g-CBT or g-RFCBT. The randomisation will be concealed from the investigator by use of an off-site computer-based randomisation. Patients are randomly assigned in blocks of variable sizes (6–10) according to a pre-study computer-generated (Microsoft Excel 2011; Microsoft Corporation, Redmond, WA, USA) randomisation list to receive one of the two treatment options.

All assessments will be conducted equally in both treatment conditions by researchers blind to randomisation. To successfully maintain the blinding throughout the trial, the researchers conducting the patient assessments will be instructed to remind the patients of the confidential nature of their treatment.

In addition, all participants will be offered clinical management and treatment with anti-depressant medication if needed, as evaluated by a highly trained and experienced psychiatrist at the outpatient service. There are no restrictions in use of anti-depressant medication in this trial, but use of anti-depressive medication and changes in type of medication or dosage will be registered.

#### Intervention fidelity

Therapists conducting the g-RFCBT and the g-CBT therapies are trained cognitive behavioural therapists with at least 7 years of experience with CBT. The therapists conducting g-RFCBT groups are trained and supervised 1 h per month by the developer of RFCBT ([name]). The therapists conducting the g-CBT groups are supervised 1 h per month by a highly trained and experienced CBT supervisor ([name]). Supervision uses videotaped sessions discussed on Skype as well as face-to-face feedback on recorded sessions.

Adherence to the clinical manuals as well as competency in conducting the therapy will be assessed by using videotapes from therapy sessions. Experts in both treatments will rate a random 10 % sample of videotapes, stratified by therapy session and groups. Adherence to the manuals will be rated by using a checklist to assess the presence of key therapy components and the absence of prohibited components for both treatments. Competence will be rated by using the Cognitive Therapy Rating Scale (CTRS) for g-CBT [30] and an adjusted version of the CTRS for g-RFCBT. For both arms, kappa statistics on inter-rater reliability will be reported.

